| 1.2            | 31 March 2011   | In yellow highlights:
Updates on Co-investigator
Change in study period duration
Additional data collection tool: Daily body temperature recording
Additional assay for blood samples
In italics: minor grammatical changes |

## SYNOPSIS

**1. Title:** *Longitudinal study of the immunogenicity of BK-SE36 candidate malaria vaccine in children and young adults that participated in the BK-SE36 malaria vaccine trial in Uganda*

### 2. Objectives:

- a) To compare long term immunogenicity of BK-SE36 malaria vaccine and antibody response to natural malaria infections in children who participated in the BK-SE36 malaria vaccine trial in Uganda.
- b) To compare malaria incidence rates and severity between volunteers who received BK-SE36 vaccine (at half or full dose) and those who received placebo or no administration (control group).

### 3. Outcome:

**1)** antibody response as a result of natural malaria infections; **2)** malaria incidence; **3)** treatment incidence density (treatments per time at risk); **4)** prevalence of malaria parasitemia and parasite density for each group that received BK-SE36 vaccine (at half or full dose) and those who received placebo or no administration (control group); **5)** change in antibody titres/epitope recognition against synthetic short peptides *spanning the whole length of SE36*.

**4. Study site:** Lira Medical Centre (LMC), Lira, Uganda

**5. Study design:** Longitudinal observational study in children who participated in the BK-SE36 malaria vaccine trial in Uganda.

**6. Participants:** BK-SE36 Phase1b Stage2 study subjects (6-20 y old) who give consent for additional 11 months follow-up period, AND additional volunteers for recruitment to achieve an equal number of subjects in the control group (*i.e.* BK-SE36 cohort ( $n=66$ ) = placebo cohort + *additional volunteers* ( $n=66$ )). These additional volunteers that did not participate in Phase 1b Stage2 trial will not be receiving any intervention/administration.

**7. Number of participants:** A total of 132 participants.

(33) subjects = administered with half dose SE36 (50 µg)

(33) subjects= administered with full dose SE36 (100µg)

(9) subjects = administered with half dose of placebo (0.5mL physiological saline)

(9) subjects = administered with full dose of placebo (1.0mL physiological saline)

(48) additional volunteers to be recruited into the control group (no administration)

**8. Expected start date:** End of 40 days surveillance period of Phase 1b, Stage2

**9. Primary completion date:** 11-months after study start

**10. Overview based on approved BK-SE36 Phase 1b trial, Stage2:**

[figure not shown]

## A. INTRODUCTION

### A1. Background:

**Burden of Malaria in Sub-Saharan Africa and Uganda.** Malaria is Africa's leading cause of mortality in children under five years of age and is responsible for 10% of the overall disease burden, 40% of public health expenditure, 30-50% of inpatient admissions, and up to 50% of outpatient visits ([www.rbm.who.int](http://www.rbm.who.int)). There are several reasons why Africa bears a large proportion of the world's malaria burden. First, most malaria infections in sub-Saharan Africa are due to *Plasmodium falciparum*, the cause of the most difficult to treat and severe form of the disease. Second, this region is also home to the most efficient malaria mosquito vectors, members of the *Anopheles gambiae* complex and those of the *An. funestus* complex. Third, most African countries are "the poorest of the poor", lacking the basic infrastructure and resources necessary to mount sustainable malaria control efforts. Uganda, where the proposed work would be located, is emblematic of the immense problem that malaria poses for African countries. Malaria is endemic in over 95% of the country, with some of the highest malaria transmission intensities reported in the world [1]. According to the 2008 World Malaria Report, Uganda ranked 6th in terms of number of malaria cases and 3rd in terms of the number of malaria deaths [2]. Malaria is the leading cause of morbidity and mortality in Uganda and is responsible for up to 40% of all outpatient visits, 25% of all hospital admissions and 14% of all hospital deaths (Uganda Ministry of Health, unpublished). The overall malaria-specific mortality is estimated to be between 70,000 and 100,000 child deaths annually, a death toll that far exceeds that of HIV/AIDS [3]. A 1995 Burden of Disease study indicated that 15% of life years lost to premature death was due to malaria and that families spend 25% of their income on malaria prevention and treatment (Uganda Ministry of Health, unpublished). Poor school performance and absenteeism due to malaria reduce chances of escaping from poverty [4]. Poor people tend to live in environments conducive to mosquito breeding and malaria transmission. Thus malaria enhances poverty, which in turn causes poor disease management, locking people in a malaria-poverty trap [5].

**Epidemiology of Malaria in Sub-Saharan Africa.** Malaria in sub-Saharan Africa is largely characterized by high rates of infection and the development of partial immunity after repeated exposure. Transmission intensity ranges from under ten to several hundred infective bites per person year, but the majority of these infections do not lead to clinical illness. The risk of developing symptomatic disease is inversely proportionate to the level of acquired immunity. Partial immunity develops through repeated exposure, leading first to protection against severe forms of disease, followed by protection against symptomatic illness [6]. The result of this phenomenon is that the burden of malaria in Africa is heavily borne by young children. Newborns are protected during the first few months of life due to the transplacental acquisition of maternal antibodies and relatively high hemoglobin F content in the infants' erythrocytes [7]. After about 3-4 months of age, protection from these factors wanes, and the infant becomes highly vulnerable to malaria, including severe disease, with an estimated 75% of malaria deaths occurring in African children under the age of 5 years [8]. However, the age at which malaria risk peaks in endemic areas of Africa varies from 1-2 years of age in areas of high transmission intensity to approximately 5 years of age in areas of low to moderate transmission intensity [9]. The risk of symptomatic malaria declines as children get older, however, school aged children are at highest risk of asymptomatic parasitemia, with chronic parasitemia resulting in anemia [10-12]. Malaria parasitemia may also impact significantly on the education and learning of school-aged children [10]. However, as the intensity of malaria transmission declines due to control efforts, it is suggested that clinical immunity will be acquired more slowly and disease burdens will shift into older age groups [13]. In addition, the high

prevalence of parasitemia in children (up to 90% at any time) creates a large reservoir for transmission [14].

***Plasmodium falciparum* and Malaria Vaccine Candidates.** *P. falciparum*, responsible for the majority of malaria deaths, is a multistage parasite invoking stage-specific host immune responses. To date, the approach to malaria vaccine development has primarily concentrated on eliciting these stage-specific immune responses. Thus, malaria vaccine candidates can be divided into (1) those that stimulate a pre-erythrocytic (sporozoite or liver) immune response, (2) those that block malaria transmission by promoting an antibody response against antigens expressed in the sexual stage within the midgut of the mosquito, (3) those that target the asexual blood stages of the parasite, with vaccines reducing the toxic effect of the infection.

Natural immunity against malaria appears to be acquired over time, requires multiple infective bites, and is lost in the absence of continued exposure. The goal of blood stage malaria vaccines is to protect against disease and death, which can be achieved through acquisition of such immunity. In spite of tremendous efforts to develop malaria vaccines for decades, an effective vaccine is not yet available.

**The Malaria Vaccine Candidate BK-SE36.** It has been demonstrated that recombinant N-terminal domain of *P. falciparum* serine repeat antigen 5 (SERA5), SE36, is a potential erythrocyte stage malaria vaccine candidate [15]. Previous immuno-epidemiological studies in Apac show that natural antibody responses to SE36 are widespread and age-dependent with adult population roughly divided into two categories: sero-positive or sero-negative to SE36 antigen. An epidemiological study in malaria patients from holo-endemic Solomon Islands suggests that there is significant correlation between lower parasitemias and higher IgG titers against SE36. An experimental study using squirrel monkeys demonstrated that vaccination with SE36 protein and aluminum hydroxide conferred protection against high parasitemia and boosted serum anti-SE36 IgG after *P. falciparum* challenge. The challenge infection also changed the epitope recognition of anti-SE36 IgG to a recognition pattern similar to those observed in people with naturally acquired immunity. In chimpanzees, SE36 plus alum was highly immunogenic with antibody titers lasting more than a year. These observations provided the impetus for the development of BK-SE36 as a malaria vaccine [15].

The target population for this particular vaccine are children at risk for clinical disease (including severe disease) due to infection with *P. falciparum*. Thus in 2005, the Research Foundation for Microbial Diseases of Osaka University launched Phase 1a clinical trial of BK-SE36 in Tsukuba City, Japan (<http://www.controlled-trials.com/isrctn/pf/78679862>). The vaccine was tested in malaria naive adults and confirmed as safe and immunogenic. Moreover, a dose was identified for further evaluation. In April 2010, a Phase 1b clinical trial commenced in Lira, Uganda (<http://www.controlled-trials.com/ISRCTN71619711>). The trial was divided into two stages. In the first stage, 56 healthy subjects aged 21-40 years were randomized to receive either BK-SE36 or placebo (physiological saline) twice at 3 weeks interval. Volunteers were followed up to more than 7 weeks after the second administration and the test vaccine at 100 µg dose was found to be safe and well tolerated. The study in children population (Stage2) is ongoing at Lira Medical Centre (LMC), Lira, Uganda and targets 84 healthy subjects aged 6-20 years.

### **Study hypothesis.**

For continued development of BK-SE36, we propose to study the long term immunogenicity of BK-SE36 malaria vaccine and antibody response to natural malaria infections and to compare malaria

incidence rates and severity between volunteers who received BK-SE36 vaccine (at half or full dose) and those who received placebo or no administration (control group). We hypothesize that:

- (1) BK-SE36 cohorts will show higher antibody titres after malaria natural infection than right after administration of BK-SE36. This phenomenon is known as a natural booster effect and an important element to be considered for vaccine strategy;
- (2) BK-SE36 cohorts will show higher antibody titres against the protective epitopes in SE36 molecule; and
- (3) Malaria incidence, severity and treatment incidence density will be lower in participants who received the BK-SE36 vaccine compared to the controls who received physiological saline or no intervention

## **A2. Justification/Significance of the Study:**

A2.1. Confirmation that SE36 malaria vaccine induced immunity can be boosted by natural infection shall give an insight into whether the vaccine can provide protection in a population exposed to natural infection with genetically heterogenous *P. falciparum*. Longitudinal observational study of anti-SE36 antibody titer, with monitoring of natural malaria infections has not yet been done both in children and adults. A longitudinal observational study comparing naturally acquired antibody responses to several malaria antigens (e.g. MSP-, AMA, etc) has not yet been carried out in a study population that has been administered with BK-SE36. The proposed study will address this gap. We anticipate that the results of this study will help in understanding immune responses due to vaccination by having appropriate malaria antigens for control/comparison.

A2.2. The study shall provide information to elucidate the duration of vaccine evoked immunity.

A2.3. The study shall provide information on the possible shift of vaccine induced epitope recognition of anti-SE36 IgG after natural infection. The change of immune status can be monitored by the comparison of reactivity of antibodies against synthetic peptides covering the entire region of the SE36 molecule between vaccinated serum without malaria infection and with malaria natural infection. The epitope recognition shift of antibody by natural infection is a new concept in malaria vaccine research. If the phenomenon is observed in humans, this *might* give an insight that the vaccine can provide protection in a population exposed to natural infection.

A2.4. We shall gather information on specific alleles of SERA5 gene that may escape from the vaccine immunity (by analyzing DNA of the parasites after vaccination and natural infection).

In this study, antibody titre and blood parasitemia of each subject will be longitudinally monitored. In addition, it would be a very important manifestation and valuable data if an increase of antibody titer is observed without malaria episode. Defining clinical endpoints for malaria vaccines has proved challenging. Blood stage vaccines are intended to block disease and not infection. Unfortunately, there are no defined protective antibody thresholds, and in the absence of an objective immune assay, the endpoint of a blood stage vaccine is often reduction of a carefully defined clinical illness specific to the site at which the trial is conducted. Likewise, there has also been insufficient capacity to definitely diagnose many suspected malaria cases since malaria disease has a variety of clinical symptoms, broad range of parasitemia, and maybe confused with other illnesses that occur in the setting of baseline levels of malaria infection. We need to define accurate interpretations of malaria disease to accurately monitor the next stages of clinical trial that defines efficacy. A definitive criteria will provide an accurate picture of the malaria situation, and guide further vaccine/treatment decisions.

The anticipated observations would propel further clinical trials.

### **A3. Objectives**

A3.1. To analyze the antibody productions quantitatively and qualitatively in volunteers who experiences natural malaria infection, and those who were not able to experience malaria infection in both vaccinated and non-vaccinated groups for obtaining a baseline data of biological effects.

A3.2. To compare malaria infection rates and severity in both of vaccinated and non-vaccinated groups for obtaining a baseline data of vaccine efficacy.

A3.3. To undertake SERA5 polymorphism study of *P. falciparum* in severe malaria incidences

### **A4. Endpoints: Primary**

A4.1. Change in titers of anti-SE36 antibody, parasitemia rates, malaria incidence, malaria treatment incidence density

### **Secondary**

A4.2. Change in antibody titers/epitope recognition against synthetic short peptides *spanning the entire sequence of SE36*. Change in antibody titres relative to other malaria antigens (e.g. MSP-1, etc) may also be used for comparison to obtain further insights about immune responses/dynamics of *P. falciparum* infection in the study population.

A4.3. Possible correlation of parasite growth inhibition in a system of Antibody Dependent *P. f.* Cellular Inhibition (ADCI) by the induced antibodies and *in vivo* malaria protection.

A4.4. *P. falciparum* SERA5 gene allelic types in vaccinated group.

A4.5. Other biological analysis with the obtained sera.

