#### At each monthly visit:

- 1 Consultation/examination of injection site (for administered subjects) if there are unresolved AEs
- 2 Consultation interview for recent illness, malaria symptoms; includes capturing malaria incidences between visits
- 3 Vital signs (temperature, blood pressure, pulse rate)
- 4 A few drops of blood sampling (by finger prick) for malaria smear, filter paper blots, and ELISA assay.
5. Blood draw (4 mls) of venous blood for serum sampling

Subjects will be assigned to fall into different consultation days. Clinic visits will be in groups. Care should be exercised whenever possible that the BK-SE36 administered cohort group can be matched to a control cohort group in the same locality for equal "bias" in malaria incidence rates.

During this follow-up period, adverse events will not be reported but malaria episodes will be documented and blood samples collected for immunological testing. Daily body temperature monitoring and recording by participants or parents /guardians will be carried out by the participants themselves at home throughout the study period. Training of participants and /or parents/guardians in the use of thermometers, reading and recording of body temperatures will be conducted during the start of the study

At the final visit:

Blood sampling (20-ml venous blood) for ADCl and ELISA assays

Passive follow-up for malaria will consist of visits to LMC trial site whenever the subject is sick. During each visit, the subject will be evaluated and a malaria smear will be done whenever malaria is suspected. During the course of evaluation for malaria, other illnesses maybe uncovered in the study subjects, such as upper respiratory infections, and other bacterial or viral infections. The pharmacy can provide subjects with common over-the-counter analgesics such as paracetamol as well as antibiotics for the treatment of minor ailments and infections. If further evaluation or treatment is necessary, the subject will be referred to the hospital arm in LMC.

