**Other trial activity/Blood sampling:**

A few drops of blood will be taken from all subjects for the following:

1. Parasitemia determination: for confirmation of parasitemia by standard microscopy
2. Filter paper blood spots: A thick blood smear is made. *P. falciparum* DNA will be amplified for molecular genotyping of SERA gene polymorphism)
3. Serum preparations for *ELISA measurements on antibody titres against SE36 as well as several malaria antigens*

Blood drawn at the final visit shall be used for the following assays as well:

4. ELISA Assays with synthetic peptides covering SE36 molecule (epitope recognition)
5. Growth inhibition studies (ADCl)
6. Other biological studies, such as HLA haplotype typing

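### The SERA5 genotyping endpoint (vaccinees only) and objective (severe malaria only) match neither each other, nor the escape question in A2.4, nor the all-subject genotyping in section D

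*Protocol*

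**What the plan says.** Four places in the protocol set the scope of the SERA5 work.

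- **A2.4 (Justification)** gives the question: "We shall gather information on specific alleles of SERA5 gene that may escape from the vaccine immunity", to be addressed "by analyzing DNA of the parasites after vaccination and natural infection". It names no unvaccinated comparator.
- **A3.3 (Objectives)** places the SERA5 polymorphism study "in severe malaria incidences". It limits by severity, not by arm.
- **A4.4 (Secondary endpoints)** reads "SERA5 gene allelic types in vaccinated group". It limits by arm, not by severity.
- **Section D** limits by neither. The monthly visit includes "A few drops of blood sampling (by finger prick) for malaria smear, filter paper blots, and ELISA assay". Under Other trial activity/Blood sampling the protocol says "A few drops of blood will be taken from all subjects for the following", and for the filter-paper spots that *P. falciparum* "DNA will be amplified for molecular genotyping of SERA gene polymorphism".

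Two further places support the wide reading. Section F allows genotyping of parasites in the study area where feasible, and Appendix 1 asks whether the study population as a whole meets different parasite genotypes.

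**The concern.** An allele escapes vaccine immunity if it is over-represented in vaccinees' breakthrough infections relative to what circulates at the same time and place. Frequencies from vaccinees alone do not show this, because an allele found in most of their infections may simply be the common local allele. Controls' infections supply the reference, and A4.4 leaves them out.

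The severity limit in A3.3 raises a different problem. The background in A1 says that partial immunity protects first against severe disease, and that school-aged children carry the highest risk of infection without symptoms. In a cohort aged 6 to 20 years, a severe-only objective is therefore likely to draw on the scarcest infections and pass over the most plentiful.

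If the study were analysed and reported by its stated objective and endpoint, it could describe alleles but could not say whether the vaccine had anything to do with them.

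**Working it through.** **Step 1. Scope, side by side.** The plan gives no genotyping figure to reproduce, so the main check is of the text.

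| Place | Arms | Severity |
|---|---|---|
| A2.4, question | no unvaccinated comparator named, but escape implies one | not limited |
| A3.3, objective | not limited | severe only |
| A4.4, endpoint | vaccinated only | not limited |
| D, blood sampling | all subjects | not limited |

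A3.3 and A4.4 differ from each other, and each is narrower than section D. A4.4 is unlikely to be shorthand for both arms, because A3.1 and A3.2 name vaccinated and non-vaccinated groups explicitly where both are meant.

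**Step 2. Denominators.** From Synopsis item 7, vaccinated = 33 + 33 = 66; control = 9 + 9 + 48 = 66; total = 132, as stated. A3.3 has no arm limit, so its denominator is 132.

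**Step 3. Yield of the severe-only objective.** The protocol gives no rate of severe malaria, so the rates p below are assumptions. Expected subjects with severe malaria = 132 × p. Chance of none = (1 − p)^132, taking subjects as independent.

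| Assumed p over 11 months | Expected | Chance of none |
|---|---|---|
| 0.5% | 0.66 | 0.52 |
| 1% | 1.32 | 0.27 |
| 2% | 2.64 | 0.07 |
| 5% | 6.60 | 0.001 |

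If these divide evenly, each group has 0.33 to 3.3 severe cases. With n cases per group and complete separation of two alleles, the two-sided Fisher p-value is 2 / C(2n, n):

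- n = 1: 2/2 = 1.0
- n = 2: 2/6 = 0.33
- n = 3: 2/20 = 0.10

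So with up to three severe isolates per group, even the most extreme result would not reach 0.05.

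**Step 4. What all infections in both groups could give.** This is an illustration. It assumes one typed infection per infected subject, a two-sided 5% level, and an allele frequency of 0.50 in controls against 0.20 or 0.30 in vaccinees. None of these values is in the protocol.

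| Share of subjects with a typed infection | Per group | 0.50 vs 0.20, Fisher exact | 0.50 vs 0.20, normal approx. | 0.50 vs 0.30, normal approx. |
|---|---|---|---|---|
| 25% | 16 | 0.28 | 0.42 | 0.21 |
| 50% | 33 | 0.66 | 0.74 | 0.38 |
| 75% | 50 | 0.85 | 0.89 | 0.53 |
| 100% | 66 | 0.94 | 0.96 | 0.65 |

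The wide scope makes a comparison possible. Its power is reasonable for a large shift in frequency if at least half of each group yields a typed infection, and modest for a smaller shift.

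**The case against.** The strongest reply is that section D already settles the matter. It plans both collection and amplification for SERA genotyping in all subjects, and monthly filter-paper sampling catches infections that are not severe. On that view the control data will exist and only the wording of two items is loose. A2.4 is also modest in aim, A4.4 is secondary, no efficacy claim rests on it, and the method of comparison may be in an analysis plan that is not shown.

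Much of this stands. A reader might infer from A3.3 and A4.4 that genotyping is confined to severe malaria in vaccinees and that the escape question cannot be answered. The protocol does not support that. The two limits sit in separate items and are nowhere imposed together, so a severe-case count based on the 66 vaccinees alone would describe a design that the protocol does not state. Under A4.4 alone, every infection in a vaccinee counts and scarcity is not the problem. The absence of an allele analysis from section E is likewise no fault here.

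The reply does not remove the conflict. Objectives and endpoints define what a study reports, and they are fixed in this document. A laboratory procedure that is wider than the endpoint does not put the controls into the endpoint. An exploratory question about escape still needs a reference frequency.

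**Conclusion.** The point holds as a conflict of scope. The objective and the endpoint for SERA5 genotyping agree neither with each other, nor with the question in A2.4, nor with the all-subject genotyping in section D. As worded, A4.4 cannot separate vaccine selection from locally circulating alleles, and this follows from the text without any assumption. As worded, A3.3 would use about 0.7 to 6.6 isolates from 132 subjects, which depends on the assumed 0.5% to 5% rate of severe malaria. The question remains answerable in principle because the samples are planned in both groups. The change is worth making because it lets the study address a question it poses itself.

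**What to change.** Reword A3.3 and A4.4 to the same scope: SERA5 allelic types in all typed *P. falciparum* infections, whatever their severity, in both vaccinated and control groups. State that allele frequencies are compared between the groups, using one infection per subject or allowing for clustering by subject, and that severe episodes are described as a subset. Add to A2.4 that controls' infections provide the reference. Since 48 of the 66 controls are added volunteers and not randomised placebo recipients, the matching by locality that section D already asks for should be kept in view when the frequencies are compared.

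Cost: no new visits or blood sampling. If section D is carried out as written, the change is one of wording; if typing had been planned only for vaccinees or only for severe cases, it adds typing of filter-paper spots already due to be collected.
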